## Methods

### Aims and Hypotheses

This study’s main goal is to determine the effects of combined cTBS over rIPL and SCRT on gesture performance and social functioning in patients with schizophrenia. In addition, we aim to investigate neurocognitive, social cognitive, motor, clinical and neural effects of both interventions as secondary outcome measures. As cTBS enhances neuroplasticity and improves use of neural resources (46, 74), we expect administration of cTBS to facilitate SCRT training effects. Additionally, we hypothesize that the expected improvement of gesture performance will have positive effects on functional outcome, as both have been reported to be linked in schizophrenia (20). At the neural level, we hypothesize that the brain activity of patients will converge to the brain activity of healthy controls after both interventions, especially within the praxis network (39, 40).

This randomized controlled trial (RCT) will include three patient groups (see Figure 1). First, group A will receive real cTBS and real SCRT. Second, group B will receive sham cTBS and real SCRT. Third, group C will receive no cTBS and sham SCRT. In this study, we will also include a fourth group consisting of healthy controls, who will be assessed twice without any intervention in between. We expect the combination of cTBS and SCRT to show positive effects on both primary and secondary outcomes in patients with schizophrenia spectrum disorders. As such, we expect group A to have superior performance over group B and C in gesture performance and functional outcome after intervention (A > B > C).

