**FIGURE 1 F1:**
[figure not shown]
Study Setup. We will randomize 72 schizophrenia patients in three different groups (24 patients per group). Group A will receive real cTBS and real SCRT. Group B will receive sham cTBS and real SCRT. Group C will receive no cTBS and sham SCRT. Both sham treatments are inactive interventions that mimic as closely as possible the real treatments. Group A and B will receive 10 cTBS sessions during the first two weeks of intervention. Additionally, Group A–C will receive 16 SCRT sessions for eight weeks. Outcomes will be measured during four different time points: baseline, after cTBS (week 2), after SCRT (week 8) and follow-up (week 32). We will also include a fourth group consisting of 24 healthy controls, who will be assessed twice (baseline and week 8) without any intervention in between.

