### Setting and Enrollment

#### Study Design

This will be a three-arm, double-blind, randomized, sham-controlled trial of add-on brain stimulation and SCRT to improve nonverbal communication skills and overall functioning in schizophrenia spectrum disorders. This single-site trial will be conducted at the University Hospital of Psychiatry and Psychotherapy, Bern.

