### Allocation and Randomization

Interventions will start in blocks as soon as 6–8 participants can be randomized to three groups: Group A, group B or group C (see Figure 1). Patients will not know which treatment they receive; they will be allocated to one of three treatment arms in a blinded manner.

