### Advantages

The design of this RCT encompasses numerous advantages. The main strength of our study is the *combination* of two interventions; coupling brain stimulation with group therapy may exert cumulative therapeutic effects in gesturing and functioning in schizophrenia (20). Additionally, cTBS enhances neuroplasticity in schizophrenia patients (46, 74) and thus, may facilitate SCRT training effects. Thanks to the two comparators (sham cTBS and sham SCRT) we can evaluate the therapeutic effects of both interventions on behavioral, clinical, and neural levels. Also, we may find insights to predictors of treatment outcome. Further, the RCT design allows elimination of selection bias in treatment assignment and enables blinding from assessors and participants. Moreover, by collecting detailed demographic information over time, we will be able to correct for age, gender, education and antipsychotic medication dosage. Longitudinal data allows exploration of change in our patients, and thus, gives insight on the longevity of treatment effects. For example, our design may shed light on factors that are essential for the transfer of coping strategies. Most importantly, we are running one of the very few RCT on SCRT to involve acquisition of neuroimaging data before and after intervention. We can directly compare neural alterations to potential behavioral changes after the interventions. If this study proves to be successful it has the potential to be beneficial for other psychiatric disorders, which exhibit similar socio-cognitive dysfunctions such as depression (93, 94).

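### Patient blinding is claimed for all three arms, but Group C has no coil sessions, so patients can be blinded only to real versus sham cTBS (A versus B)

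*Protocol article*

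**What the plan says.** Study Design describes a "three-arm, double-blind, randomized, sham-controlled trial of add-on brain stimulation and SCRT". Allocation and Randomization adds, for all three arms together: "Patients will not know which treatment they receive; they will be allocated to one of three treatment arms in a blinded manner".

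Aims and Hypotheses defines the arms. A and B both get the real SCRT and differ only in whether their stimulation is real or sham. The remaining arm is defined thus: "Third, group C will receive no cTBS and sham SCRT". On stimulation attendance, the legend to Figure 1 says: "Group A and B will receive 10 cTBS sessions during the first two weeks of intervention". On the group programme, the same legend has every patient arm attending: "Additionally, Group A–C will receive 16 SCRT sessions for eight weeks".

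The section on implementing cTBS says that sham stimulation uses a placebo coil. The section on behavioral and clinical assessments says that TULIA, the primary outcome, is scored from video by a separate examiner who is masked to group and to visit.

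**The concern.** Group C receives no sham stimulation. A patient who attends ten coil sessions in two weeks, or none, cannot be unaware of it. The statement that patients do not know their treatment is therefore wrong as written for any comparison involving C.

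The contrasts with C carry much of the trial's message. The hypothesis orders the arms A > B > C on both gesture performance and functional outcome. B versus C is the only contrast from which an SCRT effect could be read, and A versus C is the one that sets the combined treatment against control. If both are reported as double-blind, readers will give them protection against expectation that the design does not supply. This matters most for the self-reports (BAG, SNS, STTS-R) and for scales that draw on what the patient tells an interviewer, such as PANSS, BNSS, GAF, SOFAS and PSP.

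**Working it through.** **Step 1. What each patient can observe, set against what the arm receives** (Aims and Hypotheses; Figure 1 legend).

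| Arm | Attends coil sessions | Stimulation | Attends group therapy | SCRT |
|---|---|---|---|---|
| A | yes, 10 | real | yes, 16 | real |
| B | yes, 10 | sham | yes, 16 | real |
| C | no | none | yes, 16 | sham |

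**Step 2. Which contrasts can be masked to the patient for stimulation.**
- A versus B: both attend the coil, and the placebo coil hides real from sham. Masking is possible.
- A versus C: coil against no coil. Not masked for receipt of stimulation.
- B versus C: coil against no coil. Not masked for receipt of stimulation.

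So one of the three pairwise contrasts can be patient-blinded and two cannot. This follows from the arm definitions alone.

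**Step 3. Whether coil attendance also reveals SCRT status.** Coil attendance in A/B/C is yes/yes/no, and real SCRT is yes/yes/no. The match is exact: no arm pairs coil sessions with sham SCRT, and none pairs real SCRT with no coil. A patient who knows how the three arms are composed can read SCRT status from coil attendance. A patient who does not know this cannot. The article does not say what patients are told, so this step is conditional.

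**Step 4. The article's own figure.** The sample size is not affected. For the group-by-time interaction with k = 3 groups, m = 3 time points, f = 0.15, ρ = 0.75 and N = 72, sphericity assumed:
- λ = f²·N·m/(1 − ρ) = 0.0225 × 72 × 3/0.25 = 19.44
- df = (k − 1)(m − 1) = 4 and (N − k)(m − 1) = 138
- power = 0.952 at α = 0.05

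This reproduces the stated 72 patients for power 0.95.

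**Step 5. Illustration only.** Suppose expectation shifted a patient-reported change score between two arms by 0.2 to 0.3 SD with no true effect. This range is an assumption with no source in the documents. With n = 24 per arm and ρ = 0.75:
- SD of change = √(2 × 0.25) = 0.707 SD
- SE of the difference = 0.707 × √(2/24) = 0.204 SD
- df = 72 − 3 = 69
- noncentrality = 0.2/0.204 = 0.98, or 0.3/0.204 = 1.47
- false-positive rate at nominal 5%: 16.2% or 30.5%

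These numbers show only that a modest shift would matter at this sample size. They do not estimate this trial's error rate. The 0.75 is the correlation assumed for the sample size and is not given for these scales, it makes no sense for a therapy-satisfaction scale without a pre-therapy baseline, and the planned analysis is a three-group repeated-measures model, not this pairwise test.

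**The case against.** Several stronger readings are tempting, and the objections to them stand.

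- A reader might infer that coil attendance tells every patient whether the group therapy is real or sham, so that SCRT is open-label throughout. The documents do not show this. It requires patients to know that coil sessions always go with real SCRT. The sham SCRT is a substantive interactive programme of psychoeducation and mindfulness, and the Figure 1 legend says that both shams are built to resemble the real treatments. A Group C patient could know that there was no coil without knowing that the therapy was the sham.
- The Advantages section says that the RCT design "enables blinding from assessors and participants". One might take this as a further claim that every contrast is blinded. It is better read as a general remark on randomized designs, and the point does not rest on it.
- The primary outcome is largely protected. The TULIA examiner is masked to group and visit, and A versus B, which isolates cTBS, can stay patient-blind. What remains for TULIA is expectation and effort during performance.
- The functional scales are already secondary, and one of them, the UPSA-b, is performance-based. It would be wrong to treat all functional outcomes as equally exposed.
- How interviewers are masked, and whether patients are asked to guess their arm, are details that an article may leave to the full protocol. Their absence is not a fault.

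None of this reconciles an arm without any coil sessions with the statement that patients in all three arms do not know their treatment. Nothing in the article hides the missing coil sessions from Group C.

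**Conclusion.** The blinding statements in Study Design and in Allocation and Randomization are wrong as written, because they claim for the whole trial a property that the design can have only for A versus B. A–C and B–C, two of the three pairwise contrasts, are not patient-blinded for receipt of stimulation. That conclusion needs no assumption beyond the arm definitions. That these contrasts may also be unblinded for SCRT is conditional on patients having been told the make-up of the arms.

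The size of any resulting bias cannot be derived from the documents, and an inflated false-positive rate should be quoted only as an illustration. The design, the sample size and the masked TULIA rating stand. What changes is how the comparisons with C may be described and how far their patient-informed outcomes can be relied on.

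**What to change.** 1. In Study Design and in Allocation and Randomization, limit the patient-blinding claim to real versus sham cTBS. Suitable wording: patients in Groups A and B are blinded to real versus sham cTBS; the comparisons of A and B with C are not patient-blinded for receipt of stimulation and may not be for SCRT; the TULIA video rater is blinded to group and timing.
2. Rest efficacy claims for A–C and B–C mainly on the video-rated TULIA, and note that patient expectation and effort can still affect it.
3. For these two contrasts, present self-reports and patient-informed interview scales as not patient-blinded and supportive.

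An arm-guess question, or an instruction to patients not to mention stimulation to interviewers, is optional. With 36 patients past week 8 by June 2022 against 72 planned, guesses collected from then on would be partial and could not describe the whole sample.

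The cost is wording and a less favourable description of the trial. No arm, treatment or sample size changes.

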### Statistical Considerations and Plan

Assuming a medium effect size (*f* = 0.15) in a repeated measures ANOVA with moderate-high correlation between time points (0.75), a power of 0.95 and an alpha = 0.05, we will need 72 patients (24 per group). In addition, a control group of 24 healthy subjects will be required. All four groups will be compared pre-to-post with an interval of 8 weeks (see Figure 1). The main effects of the combined interventions on the primary and secondary outcomes will be calculated in a repeated measures design including 3 main time points (Baseline, week 2, and week 8) and three patient groups (A, B, and C). With the latest SPSS and R versions, we also will run additional (partial) correlations, linear regressions, MANCOVAS using covariates (e.g., age, education, and medication).

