### Limitations

This RCT entails a few limitations. First, we cannot eradicate the influence of medication; most patients suffering from schizophrenia are on antipsychotic treatment and other medication (e.g., blood pressure suppressants, antidepressants). However, for antipsychotic medication, we will control for Olanzapine equivalents in our statistical analyses. Second, we cannot eliminate gains linked to repeated test exposure as a result of retaking the same test under comparable conditions (i.e., retest effects). We counter these effects by randomizing the order of our test items for most of our assessments. Additionally, the time between most of our assessments makes training effects quite unlikely (i.e., 8 weeks, 32 weeks). Third, some of the data we collect are self-reports. Due to the subjective nature of self-reports, their psychometric aspects (e.g., reliability and validity) can be questionable or subject to biases (e.g., response bias). However, self-reports are necessary. For example, it is essential to compare patients’ subjective symptoms before and after intervention to find out if we are helping them. Fourth, another concern is the generalizability of the trial results. Participation in our study is only appropriate for a subgroup of schizophrenia patients, as it consists of 30 meetings in 3 months. As such, we can only include stable outpatients with good time management, commitment and tolerance to additional stress. This might cause the data collection to become arduous and dropout rates to be high.

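### The 0.95 power is correct for f = 0.15 on the arm-by-visit interaction scale, but that f is not a medium arm difference, for which 72 patients give less power

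*Protocol article*

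**What the plan says.** Under Statistical Considerations and Plan, the protocol article states its effect-size assumption as follows: "Assuming a medium effect size (*f* = 0.15) in a repeated measures ANOVA with moderate-high correlation between time points (0.75"). From this it concludes, with "a power of 0.95 and an alpha = 0.05, we will need 72 patients (24 per group"), that the trial is large enough. The analysis is a repeated measures design "including 3 main time points (Baseline, week 2, and week 8) and three patient groups (A, B, and C"). Under Aims and Hypotheses the authors expect group A to show "superior performance over group B and C in gesture performance and functional outcome after intervention (A > B > C"). The article gives no SD for TULIA, no difference in TULIA points, and no spacing or time course for the three arms. The word 'medium' is therefore the reader's only guide to how big the assumed effect is.

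**The concern.** In repeated measures power calculations the same letter f is used on several scales, and the verbal labels small, medium and large do not carry over from one to another. If f = 0.15 is a spread of interaction effects, and the assumed correlation already enters the noncentrality separately, the arm difference behind it can be well above what most readers understand by medium.

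What is at stake is how the result is read. A trial with 0.95 power for a medium effect and a null TULIA result would be taken to have made a medium benefit unlikely. If the power for a medium arm difference is much lower, that inference is not available.

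**Working it through.** **Inputs.** From Statistical Considerations and Plan: f = 0.15, correlation ρ = 0.75, α = 0.05, N = 72 (24 per arm), k = 3 arms, m = 3 visits. From Aims and Hypotheses: the order A > B > C. Assumed: equal baselines, sphericity, all 72 analysed, and the arm spacing and time course, shown as a range.

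**1. Reproducing the plan's figure.** For the arm-by-visit interaction, λ = f²·N·m/(1−ρ), with df (k−1)(m−1) and (N−k)(m−1).

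- λ = 0.15² × 72 × 3/0.25 = 19.44; df 4 and 138; power 0.952.
- At N = 69 power is 0.943 and at N = 71 it is 0.949, so 72 is the smallest N that reaches 0.95.
- The factor 1/(1−0.75) = 4 comes from the correlation.

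Other three-arm readings need a different N: interaction with 2 visits 90, interaction with 4 visits 63, visit main effect 60, between-arm main effect 576, f on the partial-eta-squared scale 420. A four-group, four-visit interaction also gives 72 in total. It does not fit 24 per group in three patient groups, and it is on the same interaction scale anyway.

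**2. What f means here.** It is the root mean square of the nine arm-by-visit interaction effects, divided by the between-patient SD at a visit. Let D be the largest arm difference at week 8 in SD units. Then f = D × √(mean square of the centred arm pattern × mean square of the centred visit pattern).

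- Arms evenly spaced (½, 0, −½): mean square 1/6. One arm apart: 2/9.
- Effect at baseline, week 2, week 8 growing linearly (0, ½, 1): mean square 1/6. All present at week 2 (0, 1, 1) or only at week 8 (0, 0, 1): 2/9.

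| Arms | Time course | f/D | D at f = 0.15 |
|---|---|---|---|
| Even steps | linear | 0.1667 | 0.90 |
| Even steps | (0,1,1) or (0,0,1) | 0.1925 | 0.78 |
| One arm apart | linear | 0.1925 | 0.78 |
| One arm apart | (0,1,1) or (0,0,1) | 0.2222 | 0.68 |

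With even steps the A-B difference is half of D: 0.39-0.45 SD.

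**3. The same effect on other scales.**

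- One-way f at week 8: 0.15/√(1/6) = 0.37 or 0.15/√(2/9) = 0.32.
- Partial eta squared: 19.44/(19.44 + 138) = 0.12.
- Partial f²: 19.44/138 = 0.14.

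**4. Power of the same overall test at N = 72 for smaller effects.** Here λ = 864 f², since 72 × 3/0.25 = 864.

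| Effect | f | λ | Power |
|---|---|---|---|
| A-C 0.5 SD, even steps | 0.083-0.096 | 6.0-8.0 | 0.46-0.59 |
| One arm apart by 0.5 SD | 0.096-0.111 | 8.0-10.7 | 0.59-0.73 |
| One-way f 0.25 at week 8 | 0.102-0.118 | 9.0-12.0 | 0.65-0.79 |

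A simulation with 20,000 runs agrees: 0.950 at D = 0.90 (linear), 0.953 at D = 0.78 (full from week 2), and 0.454 and 0.596 at D = 0.5 under those two time courses.

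**5. The conventional medium f on the plan's own scale.** f = 0.25 gives λ = 54 and power above 0.99; 30 patients would be enough (power 0.97). It would correspond to an A-C difference of 0.25/0.1925 = 1.30 to 0.25/0.1667 = 1.50 SD with even steps.

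**The case against.** The strongest reply is that nothing has been miscalculated: f, ρ, α, power and N are all printed and agree, and the dispute is over one adjective whose benchmarks come from outside the documents. Much of this stands.

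- **A reader might infer that 0.15 is not medium by any benchmark, or that the effect is simply large.** The figures do not support that. Partial f² of 0.14 and partial eta squared of 0.12 are near the medium or between the medium and large conventions, and the week-8 one-way f of 0.32-0.37 lies between 0.25 and 0.40. It passes 0.40 only if the denominator becomes the SD of change, √(2 × 0.25) = 0.707, which gives 0.45-0.52.
- **On the plan's own scale 0.15 is more cautious than 0.25.** This is true, and power at 0.25 exceeds 0.99. But it means that 0.15 is not the conventional medium there, and 0.25 on that scale is an A-C difference of 1.3-1.5 SD.
- **The 0.78-0.90 SD is the outermost pair only.** Also true. Adjacent arms differ by 0.39-0.45 SD, and the mean pairwise difference is 2D/3 = 0.52-0.60 SD. If 'medium' meant 0.5 SD between every adjacent pair, A-C would be 1.0 SD and the overall test would have power of 0.98 or more. That power would still belong to the overall test: a two-arm change-score comparison of A with B at 0.5 SD, 24 per arm, has about 0.67.
- **Spacing and time course are assumed.** They are, hence the ranges.

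The argument that such detail belongs in a fuller document does not help. The article makes a positive statement about power, and that statement is what needs correcting.

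**Conclusion.** The point holds as a matter of what the power figure refers to. N = 72 and power 0.95 are correct for an overall arm-by-visit interaction of f = 0.15. Calling that effect medium misdescribes it if medium means the largest arm difference: f = 0.15 implies 0.68-0.90 between-patient SD at week 8, which is medium to large. For a largest difference of 0.5 SD the power is 0.46-0.73 across the patterns examined, and for a week-8 one-way f of 0.25 it is 0.65-0.79.

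A reader might go on to say that the trial has only even odds of detecting a medium effect. That describes only the case of even steps with A-C at 0.5 SD; other patterns give up to 0.73. Nor does the check show that the sample size was computed wrongly.

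The conclusion rests on the assumed patterns, equal baselines, sphericity, complete data and conventional benchmarks. Missing data would lower these powers; under Limitations the article itself warns of participation demands that "This might cause the data collection to become arduous and dropout rates to be high".

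**What to change.** Keep N = 72 and the analysis. Delete 'medium' and restate the sentence along these lines: *72 patients (24 per group) give 0.95 power for an overall arm-by-visit interaction of f = 0.15 with correlation 0.75 between visits. Depending on the pattern, this corresponds to a largest arm difference of about 0.7-0.9 between-patient SD at week 8; power for a largest difference of 0.5 SD is about 0.46-0.73.* State the assumed arm patterns and time courses beside it.

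The cost is one sentence and a less favourable stated figure. No patients, visits or analyses are added. What changes is how much a null TULIA result can be taken to exclude.

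### The 0.95 power for 72 patients fits an undirected group-by-time interaction; it does not carry over to A > B > C or to A versus B, whose power depends on an arm spacing the protocol never states

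*Protocol article*

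**What the plan says.** The Statistical Considerations and Plan section of the protocol article gives the effect size ("Assuming a medium effect size (*f* = 0.15"), the test family and correlation ("in a repeated measures ANOVA with moderate-high correlation between time points (0.75"), and the result ("a power of 0.95 and an alpha = 0.05, we will need 72 patients (24 per group"). It does not say which effect of the repeated measures ANOVA is powered. On the analysis it says "The main effects of the combined interventions on the primary and secondary outcomes will be calculated in a repeated measures design", with three visits (baseline, week 2, week 8) and the three patient groups.

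The Aims and Hypotheses section predicts for group A "superior performance over group B and C in gesture performance and functional outcome after intervention (A > B > C". Figure 1 confirms equal allocation. A receives real cTBS with real SCRT, B sham cTBS with real SCRT, and C no cTBS with sham SCRT.

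The article gives no expected size for A versus B, B versus C or A versus C, no time course of the effect, and no power for any pairwise or ordered contrast.

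**The concern.** The sample size, the power, the analysis and the hypothesis are all stated, but they do not refer to the same test. An omnibus interaction asks whether the three groups follow different courses in any way at all. It does not ask whether A is above B.

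A and B differ only in real versus sham stimulation, so any conclusion about cTBS has to come from that pair. A reader who sees a trial described as having 95% power could take a non-significant A versus B result as good evidence against cTBS. The same reader could take a significant omnibus result as evidence for it. Neither inference is covered by the stated power.

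**Working it through.** **Inputs from the article:** f = 0.15; correlation ρ = 0.75; α = 0.05; k = 3 groups; m = 3 visits; N = 72, 24 per group.

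**Step 1: reproduce the stated figure.** For the group-by-time interaction under sphericity:

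- λ = f²·N·m/(1−ρ) = 0.0225 × 72 × 3 / 0.25 = 19.44
- df = (k−1)(m−1) = 4 and (N−k)(m−1) = 138
- Power = 0.952. The next smaller balanced N, 69, gives 0.943.

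So 72 is the smallest N that reaches 0.95. Other readings with three groups do not give 72: the group main effect has power 0.21, the time main effect 0.98, the interaction with two visits 0.894 and with four visits 0.980. Four groups with four visits also lands on a balanced 72, but that would be 18 per group, not 24.

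**Step 2: what the test can show.** λ depends on f only, not on which arm produces it. If A = B and C alone differs, with f = 0.15, power is still 0.952.

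**Step 3: convert f into differences between arms.** f² is the mean squared interaction effect over the nine cells, in units of the within-group variance. The spacing of the arms and the time course are not in the article, so both are assumptions. For equal steps d:

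- Linear over the visits (0, ½, 1): (2d²/3)(1/6) = d²/9 = 0.0225, so d = 0.45 SD.
- Effect at week 8 only (0, 0, 1), or fully present from week 2 (0, 1, 1): (2d²/3)(2/9) = 4d²/27 = 0.0225, so d = 0.39 SD.

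**Step 4: power of a week-8 pairwise test.** Noncentral t, 24 per arm, two-sided 5%. The SD is √(2(1−0.75)) = 0.707 for a change score, or √(1−0.75²) = 0.661 with baseline adjustment. For example, (0.39/0.707)·√12 = 1.91 gives 46%, and (0.45/0.661)·√12 = 2.36 gives 64%.

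| Position of B (assumed) | A–B difference, SD | Power, A versus B |
|---|---|---|
| B = C (limit) | 0.67–0.78 | 90–98% |
| one third of the way from C to A | 0.51–0.59 | 69–86% |
| halfway (equal steps) | 0.39–0.45 | 46–64% |
| two thirds of the way | 0.25–0.29 | 23–33% |
| B = A (limit) | 0 | 5% |

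B versus C is the mirror image: where A versus B has 69–86%, B versus C has 23–33%.

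**Step 5: the ordering as a whole.** At fixed f, equal spacing makes the smaller step as large as it can be, and the linear time course gives the largest week-8 difference. About 64% is therefore a ceiling for the weaker adjacent step in this test. Under equal steps, simulation of both A > B and B > C being significant gives 14–27% (change score) or 19–35% (baseline-adjusted), about 15–35% overall. A versus C has 96–99.6%.

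**Step 6: dropout.** All of this assumes 72 completers, while the Limitations section says dropout may be high. As an illustration only, 18 completers per arm would bring A versus B under equal steps to 36–51%.

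**The case against.** **The effect is not named, so the mismatch is inferred.** True, but the inference is tight: the article's own groups, visits and group size return 72 exactly.

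**A versus B is not declared the key contrast.** This stands. The main goal is the combined treatment, which A versus C addresses and for which power is high. A single-degree-of-freedom trend contrast across A, B and C would have about 99% under equal steps. So it would be too broad to say that 72 patients cannot serve the ordered hypothesis in any form. But no trend test is stated, a trend can be carried by A versus C alone, and A > B is part of the prediction.

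**Pairwise follow-up belongs in the SAP.** This is fair, and its absence from an article is not the point. The point is a power figure given beside a hypothesis that it does not cover.

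A reader might go further in three ways that the document does not support:

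- That A versus B simply has 46–64% power, or that a planned A–B effect would be missed about half the time. No A–B effect was planned, and the range holds only for equal steps.
- That a literal group main effect, averaging in baseline, will decide the trial. The same section says the groups are compared from before to after treatment, so main effects is better read as loose wording.
- That the authors will treat a significant omnibus test as support for cTBS. Nothing in the article says so.

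**Conclusion.** The point holds in this form: the 0.95 belongs to the undirected group-by-time interaction and does not transfer to A > B > C or to A versus B. At the f that justifies 72 patients, A versus B can have anything from 5% to about 98% power. It reaches 95% only when B is nearly equal to C, which conflicts with the article's own B > C. Whatever the spacing, the two adjacent steps cannot both exceed about 64%.

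These figures rest on the article's f and correlation, a two-sided 5% week-8 test, complete data and the assumed spacings and time courses shown above.

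**What to change.** 1. State that 0.95 is the power of the group-by-time interaction, and use that term in place of main effects. Report power for A versus B, B versus C and A versus C, each with its spacing assumption and range, and say that the figures are before dropout.
2. State that any claim for cTBS rests on A versus B, not on the omnibus test.
3. Prespecify baseline-adjusted week-8 TULIA contrasts with error control. One option is a three-group test at week 8 at 5% and, if significant, the three pairwise contrasts each at 5%; with three arms this is a closed procedure. A fixed sequence A–C, A–B, B–C would also control error, but it places B versus C behind A versus B. Under equal steps that cuts B versus C from 46–64% to about 15–35%.

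The cost is wording, settled before unblinded outcome data are examined. No extra patients are needed. The downside is that the stated power becomes less favourable for the adjacent contrasts, and pairwise power under the gated option can only equal or fall below the ungated figures above.
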